### Interventions

2.3

The participants included in the observation will be self-controlled, and each patient randomly selected 3 different scar treatment areas at the same site as observation specimens.

Control group: Take the untreated pathological scars of the participants as blank control. This group will not give any intervention.

Intervention group: Among the two pathological scars, group A will be treated with conventional external medicine of western medicine, and group B will be treated with oral TCM decoction combined with conventional external medicine of western medicine. The main components of the TCM prescription are: *Baizhi, Jiazhu, Leiwan, Maidong, Yuanhu, Taoren, Honghua*, and *Jingjie*. Specific treatment method: clean the scar area, apply gel to the affected area, every 3 times. TCM decoction is taken orally after meals, 3 times a day. The total application time will be 8 weeks. At the same time, closely monitor the change of the condition in order to control the deterioration of the condition in time (Fig. 2).

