**Methods/design::**

In this study, we will use our own front-to-back clinical research method. We plan to include 120 young and middle-aged female patients who meet the diagnostic criteria for pathological scars. The untreated pathological scars of the enrolled patients will be used as blank controls. The intervention group will be given conventional western medicine treatment and combined Chinese and western medicine treatment. The assessment of scar area, color, hardness, thickness, itching, and pain was recorded for 8 weeks of treatment.

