#### Inclusion criteria

2.2.2

This study will be conducted in China. Patients will be recruited from Plastic surgery departments of the Second Affiliated Hospital of Shaanxi University of Chinese Medicine. We will enroll participants based on the following inclusion criteria:

1.It meets the diagnostic criteria for pathological scars;2.There are at least 3 pathological healing scars throughout the body.3.Female patients of 16 ≤ age ≤ 40 years old;4.The time for the formation of fatigue marks exceeds 3 months;5.Those who have voluntarily signed the informed consent.

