### Randomization and blinding

2.6

Participants will be randomly allocated to the 2 groups through a sequence of numbers generated by a computer program before starting the selection process. The group assigned to each patient will be kept in a sealed envelope with the objective of concealing the assignment to the researcher, who will decide on the entry of subjects to the study. Given the nature of the interventions, the physiotherapists, and the patients, blinding will not be possible. However, the evaluator and statistician will be blinded to which group the subjects evaluated will belong.

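### As section 2.3 is written, the swallowed decoction reaches all three scars of the same patient, so the scar comparisons do not isolate its effect; sections 2.5 and 2.6 describe a different, patient-level design

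*Protocol article*

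**What the plan says.** Section 2.3 (Interventions) sets up a within-patient comparison: "The participants included in the observation will be self-controlled". On the choice of scars, the same section adds that "each patient randomly selected 3 different scar treatment areas at the same site as observation specimens". The three conditions are:

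- Blank: "Take the untreated pathological scars of the participants as blank control. This group will not give any intervention".
- A: "group A will be treated with conventional external medicine of western medicine".
- B: "group B will be treated with oral TCM decoction combined with conventional external medicine of western medicine".

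The same section says that the decoction is taken by mouth three times daily and that treatment lasts 8 weeks in total. It describes no separate periods and no washout. Two other places fit this reading. The abstract states "The untreated pathological scars of the enrolled patients will be used as blank controls", and the inclusion criteria (2.2.2) require that "There are at least 3 pathological healing scars throughout the body".

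Section 2.6 (Randomization and blinding) describes something else: "Participants will be randomly allocated to the 2 groups through a sequence of numbers generated by a computer program". Section 2.5 (Sample size calculation) matches section 2.6, with 49 patients per group raised to 60 for dropout. That gives the 120 patients named in the abstract.

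**The concern.** A cream or gel can be assigned to one scar. A swallowed medicine is assigned to the patient. If the three conditions are three scars of one woman, she takes the decoction on behalf of scar B, but scar A and the blank scar are exposed as well. The label western medicine alone no longer fits A, and the label blank no longer fits the control.

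The trial exists to learn what Chinese medicine adds to western treatment. A B-versus-A result near zero could be reported as no added benefit when the comparison had little or no chance of showing one. A B-versus-blank difference could be reported as a benefit of the combination when it reflects the topical treatment. On the same reading every participant takes the decoction, so its systemic adverse events have no comparator, although the abstract's discussion promises evidence on safety.

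**Working it through.** **The plan's own figure.** Section 2.5 gives a difference of 11 Constant–Murley points, α = 0.05, power 95% and n = 49 per group, but no SD, so 49 cannot be reproduced. Solving n = 2(SD)²(1.960 + 1.645)²/11² for the SD at n = 49, two-sided, gives SD = 11/(3.605 × √(2/49)) ≈ 15.1. SDs from 12 to 20 would give 31 to 86 per group. On dropout, 49 × 1.2 = 58.8 and 49/0.8 = 61.25; the stated 60 lies between them. None of this bears on whether the decoction effect can be isolated, but it matters for the fix.

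**Expected contrasts under section 2.3.** Let w be the topical effect, t the decoction effect on scar B, and f the share of t that reaches the patient's other scars. The documents do not give f, so it is taken over 0 to 1. Assuming the effects add, the expected improvements beyond the natural course are:

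- blank = f·t
- A = w + f·t
- B = w + t

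Therefore:

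- B − A = (1 − f)t
- B − blank = w + (1 − f)t
- A − blank = w

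At f = 1, B − A = 0 and B − blank = w, so t appears in no contrast. Without additivity, A and B still have identical exposure at f = 1, so B − A remains 0. B − blank then becomes the topical effect in a patient who is taking the decoction, which need not equal the effect of the topical treatment used alone.

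**Power of B versus A.** Suppose the test has 95% power at f = 0. Its two-sided power at other values is Φ(3.605(1 − f) − 1.960) + Φ(−3.605(1 − f) − 1.960):

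| f | B − A | power |
|---|---|---|
| 0 | t | 95% |
| 0.25 | 0.75t | 77% |
| 0.5 | 0.5t | 44% |
| 0.75 | 0.25t | 15% |
| 1 | 0 | 5% (= α) |

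**Simulation check.** The assumptions were w = t = −1 on the score scale, patient SD 1, scar SD 1, a paired t test and 4,000 replicates.

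- f = 1: mean B − A about 0.00, rejection 5.1% with 60 patients and 5.4% with 120; mean B − blank −1.00, the topical effect alone.
- f = 0.5: mean B − A −0.50, rejection 78% with 60 patients and 97% with 120.
- f = 0: mean B − A −1.0 and mean B − blank −2.0.

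A larger sample does nothing at f = 1. Between 0 and 1 it restores power, but the estimate remains (1 − f)t, and with f unknown, t cannot be recovered from it.

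**What the text suggests about f.** The Introduction describes Chinese medicine as regulating inflammatory and immune responses both body-wide and locally, and as treating the patient as a whole. Nothing there confines an oral decoction to one scar.

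**Before-after comparison.** This does not help under section 2.3, because every patient takes the decoction and change over time mixes its effect with the natural course.

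**The case against.** The strongest objection is that section 2.3 may not be the operative design. Section 2.6 randomises participants, and section 2.5 counts 60 patients per group. If A and B were groups of patients, A patients would take no decoction, B versus A would be identified, and only the blank scar in B patients would be affected. The A/B sentence in section 2.3 is garbled, and the flow chart and schedule (Figures 1 and 2) are not shown.

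This stands as a qualification. It does not remove the point: section 2.6 assigns the decoction to no named group, the only text that assigns it does so by scar, and the abstract and the three-scar criterion agree with that text. Section 2.5 also uses an outcome that is not this trial's scar score.

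A reader might infer several stronger claims that the documents do not support:

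- *The trial cannot show the decoction's effect under any reading, with 5% power at any sample size.* This needs both the within-patient design and f = 1. With partial exposure the contrast is diluted, not empty.
- *B minus blank is simply the topical effect.* That needs additivity as well as f = 1.
- *Decoction adverse events have no comparator.* This holds only if every participant takes the decoction, which sections 2.5 and 2.6 contradict.
- *The same 120 patients and an amendment to section 2.3 would be enough.* Section 2.5 has no SD and is built on another instrument, so it cannot show that, and other sections must change too.

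**Conclusion.** The concern holds for the design as section 2.3 states it, supported by the abstract and section 2.2.2. On that design A and B receive the same exposure and the blank scar is not untreated. B minus A is (1 − f)t, which is exactly 0 if the decoction acts equally on all scars. With 95% power at f = 0, power falls through 77%, 44% and 15% to 5% as f rises in steps of 0.25. The values of f are assumptions, while the zero at f = 1 follows from identical exposure and does not need additivity. The protocol also contradicts itself on the unit of allocation: scars in section 2.3, patients in sections 2.5 and 2.6. No part of the text resolves this, and it should be settled before recruitment.

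**What to change.** Reconcile sections 2.3 and 2.6 so that each component is compared at the level at which it is given:

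1. Compare the oral component between randomised patients: external medicine with versus without the decoction, on the externally treated scar, adjusted for baseline score.
2. Compare only the topical treatment between scars within a patient.
3. Do not call an untreated scar in a decoction patient a blank control. It can serve to estimate the decoction without topical treatment, against the untreated scar of patients not taking it.
4. Align the abstract, the three-scar criterion (2.2.2), the sample size (2.5) and the analysis (2.7) with this.

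**Cost.** Section 2.9 says recruitment has not started, so this is a protocol amendment with no data lost, though it reaches well beyond section 2.3. The key contrast becomes between-patient and less precise. Under the simulation's assumed SDs and before baseline adjustment, the standard error with 120 patients goes from √(2/120) ≈ 0.13 paired to √(2 × (1 + 1)/60) ≈ 0.26 between patients. The paired contrast is more precise, but for an effect diluted by an unknown amount.

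The power of 60 per group must be restated on the scar score, with a stated difference and SD. The 11 points cannot be carried over: they belong to another instrument, and the six scar items scored up to 3 give a maximum of 6 × 3 = 18.

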**Figure 2 F2:**
[figure not shown]
SPIRIT figure for the schedule of enrollment, interventions, and assessments. SPIRIT = Standard Protocol Items: Recommendations for Interventional Trials, TCM = traditional Chinese medicine.

### Outcome measures

2.4

The assessment of scar area, color, hardness, thickness, itching, and pain was recorded for 8 weeks of treatment. Assess fatigue marks once a week and save case photos.

#### Primary outcome measures

2.4.1

We will use the international scar evaluation method—“*Vancouver Scar Evaluation Scale*” as the main standard for evaluating the efficacy.

1.Color: 3 points for bright red, 2 points for light red, and disappear after pressing, 1 point for non-red or some gray, 0 points for normal skin color;2.Height of scar marks: 3 points above 9 mm, 5 mm < 2 points for height ≤9 mm, 1 point for 1 to 5 mm, 0 points for flat or slightly depressed;3.Hardness: 3 points for hard as cartilage, 2 points for hardness like rubber, 1 point for softness, normal for softness skin score: 0 points;4.Itching: 3 points for severe or persistent itching, 2 points for frequent and tolerable itching, sometimes 1 point for itching, and 0 points for no itching;5.Pain: very intense 3 points for the “hyperalgesia,” 2 points for moderate-intensity allergic pain, sometimes 1 point for pain, and 0 points for no pain;6.tightness: 3 points for strong tightness, not too tight strong and tolerable score 2 points, slight tightness score, no tightness score 0 points.

Efficacy index = (total score before treatment − total score after treatment)/total score before treatment × 100%.

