#### Efficacy evaluation

2.4.2

Refer to “*Guidelines for Clinical Research of New Chinese Medicine*.” Efficacy was evaluated by the ratio of the difference between the points before and after treatment compared to the points before treatment. Syndrome treatment efficiency = (total points before treatment total points after treatment) / total points before treatment × 100%.

1.Clinical control: clinical symptoms and signs disappeared or basically disappeared, and syndrome scores were reduced by ≥95%;2.Significant effect: clinical symptoms and signs were significantly improved, and syndrome scores were reduced by 70%;3.The signs and symptoms have improved, and the syndrome scores have decreased by ≥30%;4.Ineffective: the clinical symptoms and signs have not improved significantly, and the syndrome scores have decreased by <30%.

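### The percent-change efficacy index is graded with cut-offs that do not work on a 0–18 score: the top class needs a final score of 0, the classes overlap, and the drop needed to respond rises with baseline

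*Protocol article*

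**What the plan says.** Section 2.4.1 of the protocol article names a scar scale as the main efficacy standard. It lists six items (colour, height, hardness, itching, pain, tightness), each scored in whole points up to 3; the hardness item, for example, reads "3 points for hard as cartilage, 2 points for hardness like rubber, 1 point for softness". The section then defines one derived measure, in which the fall in the total is divided by the baseline total: "total score after treatment)/total score before treatment".

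Section 2.4.2 repeats the ratio for syndrome scores, which it does not define separately, and grades it:

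- Class 1, clinical control: "clinical symptoms and signs disappeared or basically disappeared, and syndrome scores were reduced by ≥95"%.
- Class 2, significant effect: "clinical symptoms and signs were significantly improved, and syndrome scores were reduced by 70"%, with no inequality sign.
- Class 3, printed without a label: "The signs and symptoms have improved, and the syndrome scores have decreased by ≥30"%, with no upper bound.
- Class 4, ineffective: a reduction below 30%.

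Section 2.2.2 sets no minimum scar score for entry. Section 2.7 names tests, but does not say whether the raw total, the index or the class is compared, and does not mention baseline adjustment.

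**The concern.** There are three separate weaknesses. The top class appears to ask for complete clearance by number while its words allow something short of that. The class limits, as printed, do not sort every scar into one class. And because the change is divided by baseline, the same change in points receives a different index and sometimes a different grade according to where the scar started.

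The first two affect reproducibility: two analysts given the same scores could report different response rates. The third affects interpretation: a baseline imbalance between the scars or groups being compared carries into the index and into the proportions in each class.

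**Working it through.** The plan gives no worked figure for the index or the classes, so there is nothing to reproduce first. The check enumerates all possible results.

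**Inputs.** Six items scored 0–3 (section 2.4.1) give a total of 0 to 6 × 3 = 18. No number is printed for slight tightness; 1 is assumed. The cut-offs of 95%, 70% and 30% come from section 2.4.2. The syndrome score is assumed to be this total.

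**Step 1: the 95% class.** A reduction of at least 95% leaves a residual of at most 0.05 × baseline. At the maximum baseline this is 0.05 × 18 = 0.9 point. The score moves in whole points, so the residual must be 0 at every baseline from 1 to 18. The nearest miss is 18 to 1: 17/18 = 94.4%. A residual of 1 point would need a baseline of at least 1/0.05 = 20, beyond the scale.

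**Step 2: the class limits as printed.** Exactly 70% needs 0.7 × baseline to be a whole number. Between 1 and 18 that happens only at baseline 10, with a drop of 7. A fall from 8 to 2 is 6/8 = 75%: it misses class 1, is not 70%, and lands only in class 3. Any reduction of 95% or more also satisfies at least 30%, so it meets classes 1 and 3.

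**Step 3: how many results overlap.** For baselines 1 to 18 and drops from 0 to the full baseline, the number of pairs is the sum of (baseline + 1) = 171 + 18 = 189.

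- Class 2 read as exactly 70%: 18 pairs (full clearance at each baseline) meet classes 1 and 3, and 1 pair (10 to 3) meets classes 2 and 3. That makes 19.
- Class 2 read as at least 70%: 18 full-clearance pairs plus 43 pairs from 70% to below 95%. That makes 61 of 189.

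These are counts of possible results, not expected proportions of patients.

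**Step 4: points needed to reach 30%.** This is the smallest whole drop that is at least 0.30 × baseline:

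| Baseline total | Smallest drop reaching 30% |
|---|---|
| 1–3 | 1 |
| 4–6 | 2 |
| 7–10 | 3 |
| 11–13 | 4 |
| 14–16 | 5 |
| 17–18 | 6 |

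One point is 1/3 = 33.3% at baseline 3, 1/4 = 25% at baseline 4 and 1/18 = 5.6% at baseline 18. A 3-point fall passes at baseline 10 (30%) and is graded ineffective at baseline 11 (3/11 = 27.3%).

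**Step 5: where eligible scars start.** Section 2.2.1 describes a hypertrophic scar as raised, hardened and reddish brown, with itching or pain optional. Scored as leniently as possible, that is 1 + 1 + 1 = 3; it is 4 or 5 if colour or hardness scores 2. Keloids, described with marked pain and itching, score well above this. The one-point case therefore sits at the edge of the eligible range, while the gradient in the table covers all of it.

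**The case against.** **A proportional criterion is meant to ask more of severe scars.** This stands. A reader might infer that the grade reflects how mild the scar was instead of how much it improved. The documents do not support that: a percent reduction measures benefit relative to baseline, and nothing in them says that equal points mean equal benefit. What remains is sensitivity to baseline differences and abrupt steps between adjacent baselines.

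**One point rarely counts as a response.** Also right. It does so only at baselines of 3 or less, about the floor implied by the diagnostic criteria.

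**The overlap is a drafting slip.** The descending order of the cut-offs suggests assigning the highest class met, and the missing sign may have been lost in typesetting. That is a fair guess at the intention, but no such rule is printed, and it does not resolve the conflict between 95% and the wording of class 1.

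**The syndrome score may be a different scale.** Possible. With baselines of 20 or more, a residual could satisfy 95%. The six-item total is, however, the only score the article defines, and section 2.4.2 repeats the ratio from section 2.4.1.

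**A power loss is not shown for this trial.** Agreed. Simulations assuming a 1.5-point additive difference, baseline mean 10, SD 4, pre-post correlation 0.4–0.8 and 49 independent patients per group gave power of 33–75% for percent change against 50–85% for analysis of covariance. Under one proportional effect the order reversed slightly (33–67% against 30–62%); under another it did not. None of these means, SDs, correlations or effects is in the document, and section 2.3 (three scars within each patient) conflicts with section 2.6 (two randomised groups) on what is compared. No power figure should be attributed to this trial.

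**Model details belong in an analysis plan.** Partly. The classes and the index are fixed in the protocol itself, so their defects belong here. The covariate adjustment is a recommendation, not an omission.

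**Conclusion.** The point holds as a defect in how the efficacy measure and its classes are fixed.

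- On the 0–18 total, the 95% class is reached only at a final score of 0 for all 18 non-zero baselines, against wording that allows near-complete clearance. This rests on the syndrome score being the six-item total and on slight tightness scoring 1.
- As printed, class 2 is reachable by a single baseline/drop pair, and 19 of 189 pairs meet two classes. With class 2 read as at least 70%, 61 of 189 meet more than one. The missing bounds are visible in the text without any assumption; the counts use the 0–18 total.
- The drop needed for a 30% reduction runs from 1 to 6 points across the scale, so index and grade are sensitive to baseline differences.

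It should be corrected, but it does not undermine the trial: the raw scores remain usable whatever happens to the classes. The document does not support saying that response is independent of benefit, that a one-point gain is a response for most scars, or that percent change would cost this trial a known amount of power.

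**What to change.** 1. Make the primary analysis the week-8 total (0–18), adjusted for that scar's baseline total and reported as a difference in points with a confidence interval. The model should respect whatever pairing or grouping the design finally adopts. Keep the percent index as descriptive.
2. State that the syndrome score is this six-item total, and print the score for slight tightness.
3. Write the classes as exclusive bands: clinical control; at least 70% but not clinical control; at least 30% and below 70%; below 30%. Give the third band a label.
4. Reconcile the 95% cut-off with the wording of class 1. Either define clinical control as a total of 0 and drop the near-clearance wording, or allow a stated residual of at most 1 point. If a residual is allowed, also require at least a 70% reduction; otherwise a fall from 3 to 1 (2/3 = 66.7%) would count as clinical control.

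The cost is wording in section 2.4 and a matching line in the analysis plan. The index already needs the baseline total, section 2.4 already has scars assessed weekly over the 8 weeks, and section 2.9 says recruitment has not begun. The downside is slightly less direct comparability with reports that use the guideline's percent-based grading; keeping the descriptive index largely preserves it.

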#### Efficacy evaluation

2.4.2

Refer to “*Guidelines for Clinical Research of New Chinese Medicine*.” Efficacy was evaluated by the ratio of the difference between the points before and after treatment compared to the points before treatment. Syndrome treatment efficiency = (total points before treatment total points after treatment) / total points before treatment × 100%.

1.Clinical control: clinical symptoms and signs disappeared or basically disappeared, and syndrome scores were reduced by ≥95%;2.Significant effect: clinical symptoms and signs were significantly improved, and syndrome scores were reduced by 70%;3.The signs and symptoms have improved, and the syndrome scores have decreased by ≥30%;4.Ineffective: the clinical symptoms and signs have not improved significantly, and the syndrome scores have decreased by <30%.

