TCM is currently effective in preventing and treating pathological scars and has unique advantages. Oral administration of TCM, external application of TCM, acupuncture and moxibustion, and combination of traditional Chinese and western medicine can be selected. Through the analysis of syndrome differentiation of TCM, according to the actual situation of the patient, choose the appropriate prescription medicine to improve the patient's Qi stagnation, blood stasis and meridian obstruction pathogenesis as a whole, and then achieve satisfactory results. The mechanism of TCM treatment of pathological scars is mainly to inhibit the proliferation of fibroblasts and the synthesis of collagen. At present, we should fully integrate Chinese medicine pharmacology. Strengthen the research on the treatment of pathological scars with TCM, and screen out the drugs with the exact curative effect and less side effects to inhibit the scar hyperplasia. While giving full play to the advantages of TCM treatment, we should also draw on the advantages of Western medicine treatment and carry out integrated Chinese and western medicine treatment to improve clinical efficacy and reduce the recurrence rate. Although the curative effect of TCM on pathological scars is certain, there is a problem that the standard of curative effect is not uniform. Through the consensus of the Chinese medicine industry, the release of industry guidelines for the treatment of pathological scars by Chinese medicine, and the uniform evaluation of efficacy standards, are of great significance for the study of Chinese medicine treatment of pathological scars. Therefore, in this study, we will use our own front-to-back clinical research methods to evaluate the clinical efficacy and related indicators of young and middle-aged female patients who meet pathological scars, and to find an objective and effective treatment method for pathological scars.

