### Statistical analysis

2.7

Data management uses EXCEL software to build a database, double entry, check for outstanding values, and lock. Statistical analysis will be performed using SPSS 25.0 software for statistical analysis. The normality of the measurement data is tested. The data obeying the normal distribution is Student's *t* test, which is expressed by mean ± standard deviation. The data not obeying the normal distribution is rank sum test. And marginal homogeneity test; count data are expressed by rate and composition ratio, and comparison is performed by chi-square test; repeated measurement data are expressed by mean ± standard deviation, intra-group comparison is performed by analysis of variance of repeated measurement data, and inter-group comparison is by multivariate analysis of variance (MANOVA). *P* ≤ .05 indicates that the difference is statistically significant.

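### The article names a before-after method for judging efficacy and tests within-group change, but nothing makes the efficacy conclusion rest on the planned untreated control

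*Protocol article*

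**What the plan says.** All references are to the protocol article.

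- **Method of evaluation.** The Introduction says that "we will use our own front-to-back clinical research methods to evaluate the clinical efficacy", and the Discussion repeats this. The abstract is weaker: it says only that "we will use our own front-to-back clinical research method".
- **Outcome definition.** Section 2.4.1 sets "Efficacy index = (total score before treatment − total score after treatment)/total score before treatment × 100" percent. Section 2.4.2 states that "Efficacy was evaluated by the ratio of the difference between the points before and after treatment compared to the points before treatment" and applies this ratio to four grades, of which the lowest improved one reads "The signs and symptoms have improved, and the syndrome scores have decreased by ≥30" percent. The inputs are one scar's own scores before and after treatment.
- **Control.** Section 2.3 provides a concurrent control: "Take the untreated pathological scars of the participants as blank control. This group will not give any intervention". In the same section, "group B will be treated with oral TCM decoction combined with conventional external medicine of western medicine".
- **Tests.** In section 2.7, "intra-group comparison is performed by analysis of variance of repeated measurement data". The same section plans MANOVA between groups and chi-square for count data, all under a general threshold of P ≤ .05.
- **Hypothesis.** Section 2.5 states an intervention-versus-control difference of 11 points, but on the Constant–Murley questionnaire. Section 2.4 does not list that instrument as an outcome.

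**The concern.** A before-after test asks whether the score changed over 8 weeks. It does not ask whether the treatment changed it. Here the two questions can easily have different answers:

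- Scars may enter once they are more than 3 months old (2.2.2), so some may still be maturing.
- Itching, pain and tightness make up three of the six scored items (2.4.1), and patients are not blinded (2.6), so expectation can move the total.
- Patients chosen because their scars are troublesome may regress toward their usual level.
- Bias in the other direction is also possible, because 2.2.1 describes keloids as expanding. A helpful treatment could then look ineffective against its own baseline.

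The untreated scar is in the design to remove this bias. If the efficacy statement can rest on the within-group result, the control does not do its work. A report that follows the text faithfully could present a significant within-group fall as evidence that the treatment is effective.

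**Working it through.** **1. The plan's own figure.** Section 2.5 gives 49 per group at α = 0.05 and 95% power for an 11-point difference, raised to 60. No SD is stated, so 49 can only be solved backwards: 11 × √(49/2) / (1.960 + 1.645) ≈ 15.1. The inflation to 60 lies between 49 × 1.2 = 58.8 (59) and 49/0.8 = 61.25 (62). Nothing below depends on this figure except that n = 60 is used as the group size.

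**2. What each planned analysis tests.**

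| Analysis | Where | Null hypothesis | Uses control? |
|---|---|---|---|
| Efficacy index and grades | 2.4.1, 2.4.2 | none; outcome for one scar | no |
| Intra-group repeated-measures ANOVA | 2.7 | no change over 8 weeks | no |
| Inter-group MANOVA, chi-square | 2.7 | no difference between groups | yes |

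No sentence says which of the last two rows decides efficacy. The stated method (Introduction, Discussion) matches the second row.

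**3. Size for the within-group test.** The documents give neither a spontaneous change nor an SD of change, so all such values are assumptions. The scale maximum is 6 items × 3 = 18. Take no treatment effect, n = 60, a two-sided test at 0.05 and a spontaneous fall of 1 point. The noncentrality of the paired t test is (1/SD) × √60, against a critical value of 2.00 on 59 degrees of freedom.

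| Assumed SD of change | Noncentrality | P(significant) |
|---|---|---|
| 2 | 3.87 | 0.97 |
| 3 | 2.58 | 0.72 |
| 4 | 1.94 | 0.48 |

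**4. Same question for the repeated-measures ANOVA.** This used 3,000 simulated trials with nine weekly totals, SD 3, correlation 0.4 + 0.6 × 0.85^lag (SD of the 8-week change 2.80), a linear drift common to both conditions, and the Greenhouse–Geisser correction.

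| Fall over 8 weeks (points) | Within-group, n = 60 | Within-group, n = 120 | Between-group test of change, n = 60 |
|---|---|---|---|
| 0 | 4.8% | 4.8% | 5.4% |
| 0.5 | 22% | 41% | 4.4% |
| 1 | 69% | 95% | 4.6% |
| 1.5 | 97% | 100% | 4.7% |

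**5. The grades behave differently.** A 1-point fall reaches 30% only from a baseline of 1/0.30 ≈ 3.3 or less. From a baseline of 9 it is 11%, which is graded ineffective. A separate simulation of the grades used 4,000 runs, n = 60 per group and an assumed mean true score of 10 with SD 2.5. With no drift, 8% of scars showed a fall of at least 30%; with a 10% spontaneous fall, 17% did. Compared with an equally drifting control, the false-positive rate over drifts of 0 to 30% was 4.4–5.1% for the index and 4.6–5.3% for the 30% grade. The index and grades are therefore sound once they are compared with a control.

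**6. Limit of the simulations.** Both treat the groups as independent. If the conditions are scars within one patient, a paired comparison is needed. Equal drift still cancels in it.

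**The case against.** The strongest reply is that 2.4.2 defines a response for one scar. Every change-from-baseline or responder outcome uses only that unit's own values, and the control enters when conditions are compared. Section 2.7 does plan that comparison, 2.3 supplies an untreated scar, 2.5 states its hypothesis between groups, and 2.6 blinds the evaluator and statistician.

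Most of this stands. A reader might infer that 2.4.2 is the trial's decision rule, or that efficacy will be declared without a control. The documents support neither: no passage says that a within-scar fall or a share of favourable grades establishes efficacy. Nor should the abstract be counted as tying the before-after label to efficacy; only the Introduction and Discussion do so. The high rejection rates must not be attached to the grades.

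The reply does not remove the point. The one between-group hypothesis concerns a questionnaire that is not an outcome, so the scar score has no stated controlled hypothesis.

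A second reply is that a condensed article may leave the deciding comparison to a fuller document. Silence alone would indeed be no finding. But the article is not silent: it names a before-after method for evaluating efficacy and gives within-group change its own significance test.

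**Conclusion.** The point holds in a limited form. The article states an uncontrolled way of evaluating efficacy beside a controlled comparison, and it does not say that the controlled one decides. This permits spontaneous change to be reported as efficacy; it does not show that this will happen. If the within-group test were used, a useless treatment with a 1-point spontaneous fall in 18 would appear significant in about half to nearly all trials of 60 (48% to 97% for a change SD of 4 to 2), against about 5% for a between-condition comparison. The exact rates rest on assumed drift and SD, and on equal drift in treated and control scars. The direction follows from the null hypothesis of the test and does not depend on those values.

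**What to change.** 1. **Reconcile the design first.** Section 2.3 places three conditions on scars within each patient, with an oral decoction that may reach all of that patient's scars, including the untreated one. Section 2.6 allocates participants to 2 groups. Until these are reconciled, B versus A and A versus untreated are not well-defined contrasts.
2. **Name the deciding comparison in 2.4.2 and 2.7.** State that efficacy is concluded only from the between-condition difference in the scar score, or in its index or grades. Specify a paired analysis if the conditions are scars within one patient.
3. **Make within-group results descriptive.** Report change from baseline in each condition, including the untreated one, but not as evidence of efficacy.
4. **Align the text.** In the Introduction and Discussion, describe the evaluation of efficacy as a controlled comparison.

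Steps 2 to 4 cost only wording and use data already planned; section 2.9 says that recruitment has not started. Step 1 is a design clarification and may take more than wording. The downside is that a significant within-group improvement can no longer be reported as evidence of efficacy.
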